#### Clinical Effectiveness Analysis

To account for the nested cluster structure and secular time trends inherent in the stepped-wedge design, we use 2 complementary modeling approaches. For the primary binary outcome (≥5% weight loss), a generalized estimating equations model with a logit link function will be used to compare proportions across study phases. For continuous secondary outcomes (eg, mean percentage weight change and BMI reduction), we will use a Linear Mixed-Effects Model. The model is specified as follows:

Yijk=β0+β1⋅Interventionjk+Σγk⋅Timek+Σδm⋅Covariatesijk+αj+ζij+ϵijk

Where:

Yijk represents the continuous outcome for individual i in cluster j at time k.β1estimates the treatment effect (Intervention vs Control); γk represents categorical secular time trends to isolate the intervention’s impact from time-related fluctuations; and δm denotes fixed-effect adjustments for the prespecified covariates. αj is the random intercept for the cluster (clinical unit) to account for ICC; ζij is the random intercept for the individual to account for repeated measurements over time; and ϵijk represents the residual error.

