## Methods

### Study Design

This study uses a pragmatic, open-cohort SW-CRT with a 2-month step duration. The trial spans a total observation window of 6 months across 6 clinical units at a tertiary hospital in Beijing. The SW-CRT design ensures that all participants eventually receive the intervention, fulfilling ethical requirements for this high-risk population, while the staggered rollout allows the implementation team to maintain high fidelity by providing intensive technical training for 1 wave at a time.

The trial addresses the dynamic turnover of psychiatric hospitalizations (average stay 4‐6 wk) by defining each cluster as a clinical unit rather than a fixed physical location. The research team comprises trained research assistants, certified nutritionists, and sports physicians. Participants are typically enrolled during their stable recovery phase in the ward; however, the intervention is designed to be portable. Following discharge, the intervention continues remotely, with the same clinical team providing longitudinal oversight via digital clinician dashboards. This approach enables the evaluation of the intervention across the transition from inpatient care to community-based recovery.

The 6 units were randomized into 2 waves (3 units per wave) using a matched-pair constrained randomization approach. To ensure baseline balance, units were paired based on clinical setting and demographics. Allocation was managed by an independent biostatistician via REDCap (Research Electronic Data Capture; Vanderbilt University) and remained concealed from the recruitment staff and participants.

The study timeline is structured into three distinct phases:

Baseline phase (month 1): all clusters receive usual care to establish stable baseline metrics.Transition phase (2 weeks): a staggered 2-week period for device distribution and technical training, occurring at month 1 for wave 1 and month 3 for wave 2.Intervention phase: active digital monitoring lasting 5 months for wave 1 (months 2-6) and 3 months for wave 2 (months 4-6).

This open-cohort approach accounts for the dynamic turnover of psychiatric hospitalizations, allowing for individual enrollment while maintaining randomization at the cluster level (Figure 2).

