### Sample Size Estimation

The sample size was powered based on the mean reduction in body weight (kg) to provide greater statistical sensitivity than binary outcomes. Drawing from meta-analyses of digital interventions for SMI [8] and the recent CoachToFit trial [32], a Cohen *d* of 0.40 was identified as a clinically realistic target effect size. Using PASS 2021 (stepped-wedge cluster-randomized design module) with 6 clusters and monthly repeated measurements, a total sample of 204 participants (34 per unit) provides 82% power (α=.05, 2-tailed) assuming a conservative intracluster correlation coefficient (ICC) of 0.10. This value is consistent with empirical benchmarks for metabolic outcomes in psychiatric institutional settings [43-45]. Furthermore, this sample size is sufficiently robust to detect the primary categorical outcome of ≥5% weight loss, assuming a 20% success rate in the control phase and a 40% success rate in the intervention phase (odds ratio≈2.6). Accounting for a 20% attrition rate (aligned with recent SMI trial observations), the final evaluable sample (n=163) maintains ≥75% power even under varying cluster performance, ensuring robust detection of the treatment effect under pragmatic constraints.

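### The primary logit GEE rests on six randomised units with no stated clustering level, small-sample variance correction or reference distribution; run in its usual form, its 80% intervals would cover about 60-66%

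*Protocol article*

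**What the plan says.** Study Design fixes the randomisation: "The 6 units were randomized into 2 waves (3 units per wave) using a matched-pair constrained randomization approach". The rollout is "active digital monitoring lasting 5 months for wave 1 (months 2-6) and 3 months for wave 2 (months 4-6").

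Clinical Effectiveness Analysis gives the primary model in one sentence: "a generalized estimating equations model with a logit link function will be used to compare proportions across study phases". The GEE's terms, clustering level, working correlation, variance estimator and reference distribution are not given. For continuous outcomes the same section writes out a mixed model with categorical time and two random intercepts. One of these "is the random intercept for the cluster (clinical unit) to account for ICC" and the other is for the participant. It has no unit-by-period term and no stated degrees of freedom.

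The Overview of the Statistical Plans ranks estimation above testing and reports clinical effects with 80% CIs. Covariate Adjustment and Confounder Control adds exposure duration and antipsychotic risk group as time-varying covariates, and names SAS 9.4. Sample Size Estimation powers the trial on mean weight: "a total sample of 204 participants (34 per unit) provides 82% power (α=.05, 2-tailed"), "assuming a conservative intracluster correlation coefficient (ICC) of 0.10". It then states that the sample is also adequate for the binary outcome at 20% against 40%.

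**The concern.** The GEE sandwich variance is justified by a large number of independent clusters. With six, it is biased downward and also very noisy, so a normal reference makes matters worse. Clustering on participants gives many more clusters but ignores that treatment was assigned to units, so between-unit variation is left out of the standard error.

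The interval around the primary effect is at stake. The article makes that interval its main result and picks the 80% level to avoid overinterpretation. An 80% interval is already narrower than a 95% one (1.282 against 1.960 standard errors), and under-coverage would add to the overconfidence the article wants to avoid.

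**Working it through.** **The plan's own figure.** The 82% power is for mean weight (d = 0.40, 204 participants, ICC 0.10), not for the GEE, and the stated inputs do not pin it down.
- Two-sample comparison ignoring clustering: SE = √(2/102) = 0.140; 0.40/0.140 = 2.857; Φ(2.857 − 1.960) = 81.5%. At n = 163 this becomes 72.4%.
- With a parallel design effect 1 + 33 × 0.10 = 4.3: Φ(2.857/√4.3 − 1.960) = 28%.
- Hussey-Hughes variance, six monthly periods: 32% if the 34 per unit are spread over the months, 94% with 34 different patients each month, and 88% to over 99% for a closed cohort, depending on autocorrelations the article does not give.

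None of these shows that a small-sample reference was used.

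**Simulation inputs.** From the article: 6 units × 34, wave 1 treated from month 2 and wave 2 from month 4, about 20% events, visits at months 1, 2, 3 and 6 (Outcomes and Measures) or monthly (Sample Size Estimation), ICC 0.10. Assumed: ICC on the latent scale (0.02 also tried), unit autocorrelation 1.0 or 0.8, participant-level variance or autocorrelation (0.7 in some set-ups), complete data, and the 5% threshold scored at each visit so that phases can be compared. There is no true effect.

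**Unit-level GEE, uncorrected sandwich, normal reference:**

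| Set-up | Rejection at nominal 5% | 80% CI coverage | Kauermann-Carroll, t(4), at 5% |
|---|---|---|---|
| Months 1, 2, 3, 6; ICC 0.10; working correlation near truth; 1,500 runs | 19-21% | 63-64% | 4.5-5.5% |
| Months 1, 2, 3, 6; independence; 3,000 runs | 19-20% | 63-64% | 5-6% |
| Months 1, 2, 3, 6; ICC 0.10; repeat run | 19-20% | 64% | 4.5-5% |
| ICC 0.10; independence; with and without planned covariates; 800 runs | 16-19% | 61-66% | 3-6% |
| Monthly; independence; ICC 0.02 and 0.10; cohort and cross-sectional; 1,500 runs | 17-20% | 62-65% | not run |
| Monthly; exchangeable; ICC 0.10; 500 runs | 22-24% | 60-63% | not run |

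**Where the error comes from.** In the monthly cohort set-up (ICC 0.10, unit autocorrelation 1.0, independence) the mean estimated SE is 0.338 against a true SD of 0.448, a ratio of 0.754.
- SE bias alone would give rejection 2[1 − Φ(1.960 × 0.754)] = 13.9% and 80% CI coverage 2Φ(1.282 × 0.754) − 1 = 66.6%.
- The simulated values are 18.0% and 65.2%. The remainder reflects the noise in an SE estimated from six units, which is why the reference distribution must change as well.

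**Partial remedies.**
- t(4) on the uncorrected SE: 7-9% (independence) or 9-13% (exchangeable).
- Mancl-DeRouen with z: 5-8%. With t(4): 2-3%, conservative, and 80% intervals cover 87-89%.
- Kauermann-Carroll with t(4): 3-6%. Where coverage was recorded, the 80% interval covered 79-82%.

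**Clustering on participants.** At ICC 0.10, rejection at nominal 5% ranged from 9% to 30% across set-ups. At ICC 0.02 it was 5.5-9%.

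**The mixed model.** Fitted by REML with a normal reference, it rejects 4-7% at nominal 5% and 19-21% at nominal 20% when its covariance structure is true. With unit autocorrelation 0.8 it rejects 28-30% at nominal 5%. That inflation comes mainly from the absent unit-by-period term.

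**Effect on power.** A signal giving 82% power with z has noncentrality 1.960 + 0.915 = 2.875. Against a t reference this gives about 58% on 4 df or 64% on 5 df. A signal giving 75% falls to about 52% or 56%.

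**The case against.** The strongest reply is that the article is silent, not wrong. Variance estimators and degrees of freedom are usually settled in an analysis plan, and one not shown may already name a correction. This stands as a limit: a reader might infer that the article prescribes an uncorrected sandwich, and it does not. The point survives because with six units the variance method decides whether the named estimator is usable, and the article claims adequate power for the binary outcome without that condition.

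Other stronger readings are tempting but unsupported:
- *False positives at about four times the nominal rate.* That holds at the 5% level. The plan reports 80% CIs, where the error is about 36% against 20%, or 1.8 times.
- *Every interval under-covers.* The mixed model is near nominal when its covariance structure holds, and the 95% CIs for implementation outcomes do not come from these models.
- *Too many parameters for six units, so the sandwich is singular and the analysis invalid.* The article does not list the GEE's terms, and rank deficiency of the full matrix does not by itself invalidate the variance of one coefficient.
- *A randomisation test could not reach 0.05.* If each of three pairs was split across waves, there are 2³ = 8 allocations and the smallest two-sided p is 2/8 = 0.25. But the plan proposes no such test.

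It is also fair to say that scoring the outcome repeatedly is a construction. Primary Outcome sets the assessment at month 6, when both waves are on the intervention. No variance correction supplies a concurrent control at that time; that is a separate problem.

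**Conclusion.** The concern holds in conditional form. If the primary GEE is run with the usual unit-level sandwich and a normal reference, rejection under the null is about 16-24% at nominal 5%, and the planned 80% intervals cover about 60-66%. Clustering on participants also inflates the error, to about 9-30% at ICC 0.10. The exact figures depend on autocorrelations, participant-level variance, complete data and a latent-scale ICC, none of which the article fixes. The unit-level inflation appeared in every set-up tried, including ICC 0.02. For the mixed model the case is narrower: the main weakness is the missing unit-by-period term, and it matters only if unit effects change over time.

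**What to change.** State before the analysis is completed that:
- the primary GEE clusters on the clinical unit;
- its variance is a bias-corrected sandwich (for example Kauermann-Carroll or Fay-Graubard);
- tests and intervals use a t reference on about 6 − 2 = 4 df;
- covariates in the primary GEE are kept to a minimum, with fuller adjustment as a sensitivity analysis.

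For the linear mixed model, add a unit-by-period random effect and use Kenward-Roger df. Restate the power on the same basis.

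The cost is wording and a software option; no new data are needed. Intervals become wider: moving from z to t(4) alone multiplies the 80% half-width by 1.533/1.282 = 1.20, and the corrected SE adds to that. Power will be lower than the z-based figure. Choosing Mancl-DeRouen with t(4) instead would be defensible but conservative.

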### Statistical Plans

#### Overview

All analyses will follow the intention-to-treat principle. We prioritize effect size estimation over formal hypothesis testing. Implementation outcomes, including recruitment, retention, and adherence rates, will be reported with 95% CIs. For clinical intervention effects, we will report point estimates with 80% CIs to balance precision with exploratory use, as wider intervals better reflect the preliminary nature of these estimates and minimize the risk of overinterpreting early trends. To account for the different intervention durations between waves, intervention exposure duration (time since crossover) will be included as a time-varying covariate in the mixed-effects models. This approach allows for the estimation of the intervention effect while adjusting for the varying lengths of exposure across clusters.

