Several limitations warrant critical examination regarding the study’s external validity. First, the smartphone ownership requirement introduces a significant selection bias. By excluding individuals without mobile devices, we likely omitted the most socioeconomically marginalized patients and those with the most severe cognitive impairments or functional decline, who are often at the highest risk for metabolic syndrome. Consequently, our findings may overestimate the effectiveness of digital interventions in the broader SMI population where digital literacy and device access remain major barriers.

Second, a potential limitation is the transition from a cluster-based environment to individual remote monitoring post discharge. However, this reflects the real-world scenario, and our use of mixed-effects modeling robustly handles the resulting open-cohort structure and varying exposure durations. Last, the single-center recruitment at a premier tertiary psychiatric hospital in Beijing may constrain generalizability. Participants at such a specialized center may have higher educational levels, better familial support, and access to more comprehensive baseline care than those in rural or community-based settings in China. Therefore, the successful implementation observed here might not be immediately replicable in resource-limited primary care environments. Future multicenter trials involving diverse geographic and socioeconomic regions are essential to validate these findings across the full spectrum of psychiatric care settings. Nonetheless, our findings provide a critical baseline for these future comparative studies.

While we acknowledge the selection bias toward digital-literate patients and the single-center nature of this trial, this study serves as a preliminary proof-of-concept. It explores how national policy goals can be operationally adapted for the psychiatric population—a group often overlooked in general health campaigns. Rather than a finalized standard operating procedure, this trial provides initial evidence on the feasibility of digital self-monitoring. These findings are a critical first step toward developing more inclusive, multicenter strategies that could eventually inform the integration of physical health management into the “Basic Public Health Service” for patients with SMI, provided the digital divide identified in our limitations can be bridged.

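### The mixed model for weight and BMI has no unit-by-period random effect, so its 80% intervals are too narrow if units drift apart between periods

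*Protocol article*

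**What the plan says.** Under Clinical Effectiveness Analysis, for continuous secondary outcomes the article states that "we will use a Linear Mixed-Effects Model", and it gives the equation. Intervention carries the indices j (unit) and k (time). The unit term "is the random intercept for the cluster (clinical unit) to account for ICC" and carries only j. The participant term "is the random intercept for the individual to account for repeated measurements over time" and carries only i and j. The remaining random term is the residual. The time effect γk "represents categorical secular time trends to isolate the intervention’s impact from time-related fluctuations" and is common to all units.

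The Overview of the Statistical Plans and the section on covariate adjustment add exposure duration and antipsychotic risk group as time-varying covariates, which are fixed effects. The listed sensitivity analyses concern missing data and medication possession. No robust variance is stated for the mixed model.

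For clinical effects the Overview says that "we will report point estimates with 80% CIs to balance precision with exploratory use". The sample size rests on mean weight reduction, "assuming a conservative intracluster correlation coefficient (ICC) of 0.10", with no second correlation for different periods. The Discussion states that "our use of mixed-effects modeling robustly handles the resulting open-cohort structure and varying exposure durations".

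**The concern.** A constant unit intercept says that two patients of the same unit are equally correlated whether they are measured in the same month or months apart. The article itself describes short stays, continuous recruitment, turnover and a move from ward to remote follow-up, so a unit's mean could move between periods in a way other units' means do not. Treatment switches at the unit-by-period level, so such movement is noise in the treatment comparison and belongs in its standard error. The written model puts it into the participant-level residual, where it is averaged over participants as if independent.

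At stake is the precision claimed for weight and BMI change. Weight change is the outcome the trial was powered on, and the plan ranks estimation with intervals above testing, so interval coverage is the main inferential product.

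**Working it through.** **The stated power.** The article gives 82% for d = 0.40, ICC 0.10, 6 units and 34 participants per unit. A stepped-wedge calculation with monthly periods gives 32% if each unit's 34 participants are split over the months, 94% with 34 different participants each month, and 98.7% or more for a cohort of 34 with within-participant correlation of at least 0.3. An individually randomised comparison of 102 with 102 and no ICC gives 81.5%. Participants per unit-period and within-person correlation are not stated, so 82% is neither confirmed nor refuted.

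**Inputs from the article.** Six units in two waves of three; visits at months 0, 1, 2, 3 and 6; wave 1 treated in months 2 to 6, wave 2 in months 4 to 6; ICC 0.10; 34 participants per unit.

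**Assumed, because not given.** Within-person correlation 0.7; between-period unit correlation r from 0.95 to 0.8; n participants per unit-visit, either 34 (everyone at every visit) or 8. The figure of 8 comes from spreading enrolment evenly over about 25 months (May 2023 to June 2025) with 6 months of follow-up each: 34 × 6 / 25 ≈ 8.

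**True variances (total 1).** Unit 0.10r; unit-by-period 0.10(1 − r); participant 0.7 − 0.10r; residual 0.2 + 0.10r.

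**What the written model estimates instead, with P = 5 visits.** Residual c = true residual + unit-by-period variance = 0.30. Participant b = true participant − (unit-by-period)/P. Unit a = true unit + (unit-by-period)/P.

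**Standard errors.** With fixed time effects, the information lies in the wave 1 minus wave 2 differences, whose treatment pattern over the five visits is x = (0, 0, 1, 1, 0). Let A = a + b/n, B = c/n and φ = 2A/(B + 5A).

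- Model variance = (2/3) × B / (2 − 2φ).
- True variance of the same estimator = (2/3) × [A′(2 − 5φ)² + B′(2 − 4φ + 5φ²)] / (2 − 2φ)², where A′ = true unit + true participant/n and B′ = unit-by-period + true residual/n.

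**Example, n = 8, r = 0.8.** a = 0.084, b = 0.616, c = 0.30, so A = 0.161, B = 0.0375, φ = 0.382. Model variance = 0.025/1.236 = 0.0202, SE 0.142. A′ = 0.1575, B′ = 0.055; true variance = 0.0294, SE 0.171. Ratio 1.21.

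**Example, n = 34, r = 0.8.** A = 0.102, B = 0.0088, φ = 0.393. Model SE 0.070. A′ = 0.098, B′ = 0.028; true SE 0.124. Ratio 1.78.

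Coverage of a nominal 80% interval is 2Φ(1.2816/ratio) − 1.

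| r | n = 8: model SE, true SE | Ratio | Coverage | n = 34: model SE, true SE | Ratio | Coverage |
|---|---|---|---|---|---|---|
| 1.00 | 0.142, 0.142 | 1.00 | 80% | 0.070, 0.070 | 1.00 | 80% |
| 0.95 | 0.142, 0.150 | 1.06 | 78% | 0.070, 0.087 | 1.24 | 70% |
| 0.90 | 0.142, 0.158 | 1.11 | 75% | 0.070, 0.101 | 1.45 | 62% |
| 0.80 | 0.142, 0.171 | 1.21 | 71% | 0.070, 0.124 | 1.78 | 53% |

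**Wider assumptions (ICC 0.10, r from 0.95 to 0.8).** The within-participant correlation is here taken as the participant share of within-unit variance. With a cohort of 34 the ratio is 1.16 to 1.54 at 0.5, and 1.37 to 2.07 at 0.8. If the 34 are split over the visits and nobody is measured twice, it is only 1.01 to 1.05.

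These figures are asymptotic in the number of units and leave out the exposure-duration covariate.

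**The case against.** A unit intercept plus a participant intercept is a recognised stepped-wedge cohort model. Changing membership is partly absorbed by the participant intercept. Stays average 4 to 6 weeks and follow-up then moves to the home, so patients of one unit share a ward environment for only part of the time. If visits are timed from each patient's own enrolment, patients at the same visit number need not share a calendar shock at all. No passage documents unit-specific drift. All of this stands: it limits the size, and it makes the point conditional.

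One could also say that such detail belongs in an analysis plan not shown. That holds for the degrees-of-freedom method. It does not hold for the random effects, because the article writes the model out term by term.

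Three stronger readings are tempting, and the article does not support them:

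- A reader might infer that 82% power, being lower than the written model gives with 34 per unit-visit, shows that drift was allowed for or is needed. With no drift at all and 8 per unit-visit (within-person correlation 0.7), the model SE is 0.142 and power is Φ(0.40/0.1424 − 1.96) ≈ 80%. The stated power is no evidence about drift.
- A reader might take the 34-per-visit ratios as the expected error. They assume that every participant is present at every visit, which continuous recruitment over about two years makes doubtful.
- A reader might extend the point to the primary outcome. That outcome is analysed by generalized estimating equations and not by this model.

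**Conclusion.** The point holds as a conditional one. The model as written makes no allowance for unit-specific movement between periods. Where such movement exists, its standard errors came out too small in every scenario examined. Whether the error is minor or large cannot be settled from the article, since the between-period unit correlation, the within-person correlation and the number of participants per unit-period are all unstated. The Discussion's claim that the mixed model copes robustly with the open cohort is therefore stronger than this model supports. The consequence is confined to the continuous outcomes. Because the remedy is cheap and harmless when there is no drift, the change is worth making, but it is an improvement and not a correction of a demonstrated error.

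**What to change.** Add a random unit-by-period intercept to the mixed model, with the same period index k as the Intervention term, and use a small-sample degrees-of-freedom correction such as Kenward-Roger. In the planned SAS software this is one further RANDOM statement. If the variance is estimated as zero, the current model returns.

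As a check, analyse the unit-by-period means with unit, period and treatment terms. With 6 units and 5 periods this leaves 30 − 6 − 4 − 1 = 19 degrees of freedom, and fewer once exposure duration is included.

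The Results section says that initial analysis is in progress, so the change should be recorded as an amendment, or as a declared sensitivity analysis, before results are reported. The cost is wider intervals for weight and BMI when unit means do drift.
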